### Randomization and allocation concealment

Participants will be randomized to the LLLT or acupuncture group in a 1:1 ratio using a computer-generated randomization sequence created by an independent statistician using SPSS (version 26.0). Randomization will be stratified according to baseline insomnia severity (mild: ISI 8–14; moderate: ISI 15–21) to ensure balanced distribution across groups. Allocation concealment will be maintained using sequentially numbered, opaque, sealed envelopes prepared and safeguarded by the independent statistician. After baseline assessments and confirmation of eligibility, the study coordinator will open the next envelope in sequence to assign the participant to a treatment group. The statistician responsible for generating and guarding the randomization list will have no involvement in clinical assessments, intervention delivery, or outcome analysis.

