### Sample size calculation

The sample size was formally powered based on the primary outcome, which is the detection of a clinically and statistically significant difference in ISI scores between the two groups. In our single-arm pilot study of wearable LLLT involving 33 participants, the baseline ISI score was 15.12 ± 3.72 and the post-intervention ISI score after the 2-week intervention was 10.91 ± 4.44, corresponding to a mean reduction of 4.21 points. For the manual acupuncture comparator, a randomized controlled trial reported a mean ISI score of 13.4 ± 3.9 in the acupuncture group at 2 weeks post-treatment (baseline 17.1 ± 4.1)5. Because directly comparable head-to-head change-score data for wearable LLLT versus manual acupuncture were unavailable, the sample size calculation was based on post-treatment ISI means from our pilot LLLT data and a published acupuncture trial. This approach was used as a pragmatic estimate for the expected between-group difference at the primary endpoint, while the primary analysis will adjust for baseline ISI using ANCOVA. To establish superiority, we assumed a conservative between-group difference of 2.5 points in favor of the LLLT group. Using a two-sample t-test allowing unequal variances in PASS software (version 21.0.3), with a two-sided significance level of 0.05 and 80% power, the required sample size was calculated to be 90 participants, with 45 participants per group. Allowing for an anticipated 15% dropout rate to maintain statistical power, the final target sample size was set at 106 participants, with 53 participants per group.

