### Statistical analysis

All analyses will be performed using SPSS (version 26.0) or equivalent software. Two-tailed p-values < 0.05 will be considered statistically significant. The primary analysis will strictly follow the intention-to-treat (ITT) principle. For the primary superiority outcome, analysis of covariance (ANCOVA) will be employed. Although the primary endpoint is defined as the change in ISI from baseline to week 2, ANCOVA will be performed with the week-2 ISI score serving as the dependent variable, the treatment allocation (LLLT vs. acupuncture) as the fixed factor, and the baseline ISI score as a covariate (31). This approach is statistically equivalent to comparing change scores while providing better precision. Furthermore, this adjustment for baseline ISI is specifically chosen to align with the stratified block randomization procedure, thereby maximizing statistical power and precision in estimating the treatment effect.

Between-group differences in adjusted mean changes and their 95% confidence intervals (CIs) will be reported. Statistical superiority of LLLT over manual acupuncture for the primary endpoint will be considered supported if the two-sided p-value for the between-group difference is less than 0.05 and the entire 95% CI of the difference excludes zero in favor of the LLLT group (32).

The longitudinal trajectory of ISI across post-randomization assessments will be analyzed as a supportive repeated-measures analysis using a linear mixed-effects model. The model will include treatment group, time, and the group × time interaction as fixed effects, baseline ISI as a covariate, and participant-specific random intercepts to account for within-subject correlations. This model will be used to evaluate whether the between-group difference in insomnia severity is maintained at week 6.

Secondary continuous outcomes assessed at week 2 only, including PSQI, FSS, PHQ-9, GAD-7, and HRV indices, will be analyzed using analysis of covariance, with the week-2 value as the dependent variable, treatment group as the fixed factor, and the corresponding baseline value as a covariate. When model assumptions are markedly violated, appropriate transformations or non-parametric methods will be considered. A per-protocol analysis including participants with adequate adherence, defined as attending at least four of six sessions and having no major protocol deviations, will be performed as a sensitivity analysis.

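### The secondary-outcome ANCOVAs leave out baseline ISI, the stratification factor; where ISI is prognostic beyond the outcome's own baseline, their standard errors are somewhat too large

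*Protocol article*

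**What the plan says.** The Randomization and allocation concealment section fixes equal allocation and one stratification factor: "Randomization will be stratified according to baseline insomnia severity (mild: ISI 8–14; moderate: ISI 15–21".

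The Statistical analysis section gives the primary model as an ANCOVA of week-2 ISI on treatment, "and the baseline ISI score as a covariate (31", and offers a reason for the covariate: "this adjustment for baseline ISI is specifically chosen to align with the stratified block randomization procedure, thereby maximizing statistical power and precision". The supportive mixed model for ISI also carries baseline ISI.

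The same section then turns to the sleep-quality, fatigue, mood and HRV measures and assigns them an ANCOVA too. The terms of that model are spelled out: "with the week-2 value as the dependent variable, treatment group as the fixed factor, and the corresponding baseline value as a covariate". No ISI or stratum term is listed for them, and no reason is given for the difference from the primary model.

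**The concern.** For the ISI, the outcome's own baseline and the stratification variable are the same quantity, so one covariate does both jobs. For every other outcome they are different variables. Carrying over the own-baseline template therefore drops the stratification factor.

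Stratified allocation balances the ISI categories between the arms. A model without ISI leaves in the residual any variation that ISI would explain, and gives no credit for the balance that the design has secured. If ISI is prognostic given the own baseline, the reported standard error overstates the true variability of the treatment estimate, and some attainable precision is also forgone. At stake are secondary confidence intervals that are somewhat wider than necessary and secondary tests that run below their nominal level.

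A prognostic role is plausible for some outcomes. The PSQI looks back one month, so the week-2 score still covers the two weeks before treatment that the baseline ISI rates. The protocol itself chose ISI severity as its only stratification factor.

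**Working it through.** **1. The plan's own figure.** The protocol gives no precision or power figure for secondary outcomes. Its one design figure is the primary sample size: "we assumed a conservative between-group difference of 2.5 points in favor of the LLLT group", "with a two-sided significance level of 0.05 and 80% power", with SDs of 4.44 (LLLT pilot) and 3.9 (published acupuncture trial).
- Root-mean-square SD = √((4.44² + 3.9²)/2) = 4.179.
- The normal approximation gives 44 per group. The unequal-variance t-test has power 79.2% at 44 and 80.1% at 45, hence 45 per group and 90 in all.
- Dropout: 90/0.85 = 105.9, hence 106.

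The figure reproduces, and nothing below changes it.

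**2. Approximate size of the effect.** Let r be the partial correlation of baseline ISI with the week-2 outcome, given the own baseline. Adding ISI multiplies the residual variance by (1 − r²), so the standard error falls by 1 − √(1 − r²).
- r = 0.2: 1 − √0.96 = 2.0%
- r = 0.3: 1 − √0.91 = 4.6%
- r = 0.4: 1 − √0.84 = 8.3%

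**3. Break-even.** With 90 analysed, the present model (intercept, treatment, own baseline) has 87 residual degrees of freedom; with ISI it has 86. The expected model variance is unchanged when (1 − r²) × 87/86 = 1, that is r² = 1/87 and r ≈ 0.11. Below that, the extra term gains nothing.

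**4. Simulation under stratified allocation.** N = 90, 1:1 permuted blocks within the two ISI strata, 8,000 replicates per scenario. Assumed, because the protocol gives none of them: block size 4, correlation of ISI with the own baseline 0.4, correlation of the own baseline with the week-2 value 0.5, and r itself. Arrows run from own baseline only to own baseline plus continuous ISI.

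| r | Mean model SE | Fall in SE | Power, % | Type I error, % |
|---|---|---|---|---|
| 0 | 0.1828 → 0.1833 | −0.3% | 80.0 → 79.6 | 5.0 → 5.1 |
| 0.1 | 0.1829 → 0.1824 | 0.3% | 79.9 → 79.9 | 4.8 → 4.9 |
| 0.2 | 0.1832 → 0.1797 | 1.9% | 80.8 → 82.1 | 4.7 → 4.8 |
| 0.3 | 0.1834 → 0.1751 | 4.5% | 80.3 → 83.2 | 4.5 → 4.9 |
| 0.4 | 0.1835 → 0.1683 | 8.3% | 81.3 → 86.4 | 3.8 → 4.7 |

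The Monte Carlo standard error of a 5% rejection rate is √(0.05 × 0.95/8000) = 0.24 points. The fall to 3.8% is therefore clear, while 4.7% and 4.8% cannot be told apart from 5%.

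**5. Two effects inside the fall in SE.** The actual spread of the treatment estimates over null replicates moves less than the reported SE:
- r = 0.2: 0.1810 → 0.1795 (0.8%)
- r = 0.3: 0.1786 → 0.1746 (2.2%)
- r = 0.4: 0.1746 → 0.1672 (4.2%)

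At r = 0.4 the unadjusted model reports 0.1835 against a true spread of 0.1746, which is 5% too large. About half of the fall at r = 0.3 and 0.4 is thus a reported SE that was too large, and the rest is a real gain in precision.

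**The case against.** An ANCOVA on the outcome's own baseline is a valid model. The alignment argument is made for the primary analysis only, and the protocol nowhere promises the stratification factor in the secondary models, so it does not contradict itself. That stands. The protocol's own reasoning simply has not been carried through to outcomes where it would apply.

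A reader might infer that every secondary analysis definitely loses precision. The protocol does not support this, because the loss depends on a correlation that it does not report. Eligibility restricts ISI to 8–21 and PHQ-9 and GAD-7 to below 10, which tends to weaken correlations, and the own baseline may already absorb much of what ISI would explain. Nothing in the document links baseline ISI to the finger-sensor HRV indices. This objection stands in full, and it is why the point is conditional.

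A reader might also infer that the secondary results would be biased or open to false positives. They would not: the error is conservative.

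Finally, little hangs on these analyses. The trial is powered on ISI, superiority is judged on ISI alone, HRV is called exploratory, and the week-2 PSQI is to be read with caution. That keeps the point minor but does not remove it, since the term costs almost nothing.

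The omission cannot be put down to detail left for a separate analysis plan, because the secondary model is written out with its covariate.

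**Conclusion.** The point holds in conditional form and is minor. The secondary models do not reflect the stratified randomisation, although the protocol gives that alignment as a reason for the primary model. Where baseline ISI is prognostic beyond the own baseline, reported standard errors exceed what the adjusted model would give. For assumed partial correlations of 0.2 to 0.4, adding ISI saves about 2% to 8% of the SE and 1 to 5 points of power; at or below about 0.11 it saves nothing.

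The size rests on the assumed correlations and on the simulation settings listed above. The direction, conservative where there is any effect, does not depend on the exact values. Treatment estimates, the primary ANCOVA, the mixed model for ISI and the sample size are untouched.

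**What to change.** Before unblinding, specify each secondary ANCOVA as: week-2 value ~ treatment + own baseline + continuous baseline ISI. If the term is to be left out for some outcomes, HRV for example, say so and give the reason.

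Continuous ISI is preferable to the two-level stratum. At r = 0.4 the mean model SE was 0.1683 with the score and 0.1738 with the stratum.

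The cost is one of about 87 degrees of freedom and a sentence in the analysis plan. Baseline ISI is needed for eligibility, so every randomised participant should have it. The Trial status section reports that no comparative outcome analysis has been done and that statisticians remain blinded, so the term can still be added without appearing data-driven.

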Physical examination/safety check	×		×				
Interventions							
LLLT group		3 sessions	3 sessions				
Manual acupuncture group		3 sessions	3 sessions				
Outcome assessments							
ISI	×		×				×
PSQI	×		×				
FSS	×		×				
PHQ-9	×		×				
GAD-7	×		×				
HRV	×		×				
Process and safety monitoring							
Sleep diary	×	×	×	×	×	×	×
Adverse event monitoring		×	×	×	×	×	×
Concomitant medication recording	×	×	×	×	×	×	×
Dropouts/withdrawals		×	×	×	×	×	×
Participant adherence		×	×				

× indicates that the item is performed or assessed at the corresponding time point. LLLT, low-level laser therapy; ISI, Insomnia Severity Index; PSQI, Pittsburgh Sleep Quality Index; FSS, Fatigue Severity Scale; PHQ-9, Patient Health Questionnaire-9; GAD-7, Generalized Anxiety Disorder-7; HRV, heart rate variability. Week 0 indicates baseline, week 2 marks the end of treatment, and week 6 represents follow-up. Both interventions are delivered three times per week for 2 weeks, with six sessions in total. ISI is assessed at baseline, week 2, and week 6; PSQI, FSS, PHQ-9, GAD-7, and HRV are assessed at baseline and week 2. Sleep diaries, adverse events, concomitant medications, dropouts/withdrawals, and adherence are monitored as indicated.

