### Treatment fidelity and adherence

To promote intervention fidelity, all practitioners and staff will receive standardized training before the trial. To improve positioning reproducibility across sessions, bilateral HT7, PC6, and SP6 will be re-identified at each treatment session using standardized anatomical landmarks by the same trained research personnel whenever possible. The irradiation outlets will be aligned with the marked acupoint sites before activation, and direct skin contact will be maintained throughout the session. Adjustable elastic straps and adhesive single-point irradiation modules will be used to minimize displacement and variability in positioning. The position and contact condition of each module will be checked at the beginning of treatment and, when necessary, during the session to maintain consistent alignment and skin-contact conditions across sessions. Checklists will be used during sessions to record adherence to operating procedures. Attendance at each treatment session will be recorded. Participant adherence will be monitored using attendance logs and brief compliance interviews, and reasons for missed sessions will be documented.

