### Outcomes

#### Primary outcome

The primary outcome is the change in Insomnia Severity Index (ISI) total score from baseline to the end of the two-week intervention (week 2). The ISI is a 7-item self-report scale that assesses the severity of nocturnal and daytime components of insomnia over the past two weeks, with total scores ranging from 0 to 28. Higher scores indicate more severe insomnia. The ISI has been validated in Chinese populations and demonstrates good reliability and sensitivity to change (20, 21).

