For the primary ANCOVA analysis, missing week-2 ISI data will be handled using multiple imputation under the missing-at-random assumption. The imputation model will include baseline characteristics, treatment allocation, and available outcome data, and results from imputed datasets will be combined using Rubin’s rules (33). For the supportive longitudinal ISI analysis, the linear mixed-effects model will use all available ISI observations under the same missing-at-random assumption. For secondary outcomes assessed at week 2 only, missing data will be handled using multiple imputation if the extent of missingness is substantial, and complete-case or imputation-based sensitivity analyses will be conducted as appropriate.

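### The imputation model for week-2 ISI, as listed, holds only baseline data and arm for anyone lost before week 2; the week-1 diary and attendance already being collected should be named as auxiliary variables

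*Protocol article*

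**What the plan says.** The Primary outcome section states: "The primary outcome is the change in Insomnia Severity Index (ISI) total score from baseline to the end of the two-week intervention (week 2"). The Statistical analysis section analyses it by ANCOVA of week-2 ISI on arm and baseline ISI, with missing week-2 values multiply imputed under missing at random. The contents of the imputation model are given in one sentence: "The imputation model will include baseline characteristics, treatment allocation, and available outcome data".

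The footnote to Table 3 fixes when outcomes exist: "ISI is assessed at baseline, week 2, and week 6; PSQI, FSS, PHQ-9, GAD-7, and HRV are assessed at baseline and week 2". The same table marks a sleep diary in every week from 0 to 6 and participant adherence in weeks 1 and 2, both under the block "Process and safety monitoring" and not in the block of outcome assessments. Under Treatment fidelity and adherence the protocol adds: "Attendance at each treatment session will be recorded", and also that "reasons for missed sessions will be documented".

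The Sample size calculation section gives the expected loss: "Allowing for an anticipated 15% dropout rate to maintain statistical power", which takes 90 participants to 106.

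**The concern.** Imputation under missing at random improves on dropping incomplete cases only when its model holds information that the analysis model lacks. For someone who leaves during treatment and does not return, the scheduled outcomes supply nothing after baseline. The supportive mixed model gives no check, because it uses ISI observations only, and such a participant has none after randomisation.

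The Blinding section concedes that participants know their treatment and that the primary outcome is self-reported. Leaving early because sleep is not improving could therefore be more common, or work differently, in one arm. Missing at random would then fail given baseline and arm, yet be closer to true given week-1 sleep and attendance. What is at stake is a bias in the primary comparison that data already scheduled could reduce.

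**Working it through.** **1. The plan's own figures.** Inputs from the Sample size calculation section: difference 2.5, SDs 4.44 and 3.9, two-sided 0.05, 80% power. An unequal-variance t-test gives 79.2% power at 44 per arm and 80.1% at 45, so 45 per arm reproduces. Then 90 / 0.85 = 105.9, rounded up to 106. Nothing in this point changes these figures.

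**2. How many could be affected.** 0.15 × 53 = 7.95, so about 8 per arm, or 0.15 × 106 = 15.9, about 16 in all. This is an upper figure at the planned rate. The protocol does not say how many would be lost for good before week 2.

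**3. What the listed model contains for each pattern of missing data.**

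- Misses the week-2 ISI but completes other week-2 scales: those scales are outcome data and can be used.
- Misses week 2 but returns at week 6: the week-6 ISI is outcome data and can be used.
- Lost for good before week 2: baseline and arm only.

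**4. What imputation then adds in the third pattern.** When the imputation model has the same predictors as the ANCOVA, it redraws the missing values from the line fitted to the completers. A simulation checked this with 53 per arm, about 15% dropout, 20 imputations and 800 runs per setting. It assumed a residual SD of 3.6 and a week-1 diary score correlating r with the week-2 ISI residual. The bias from imputation on baseline and arm agreed with that of complete-case ANCOVA within 0.01 in every setting (in the random-dropout setting, SE about 0.77 against 0.76).

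**5. Size of the bias in that simulation, in ISI points, at r = 0.3 / 0.5 / 0.7.** Dropout was logistic in the diary score.

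| Dropout mechanism (assumed) | Baseline and arm only | Diary added |
|---|---|---|
| Unrelated to diary | 0.04 / 0.02 / 0.02 | 0.03 / 0.01 / 0.02 |
| Same relation in both arms | 0.02 / 0.01 / 0.00 | 0.01 / 0.02 / 0.00 |
| Poor responders leave LLLT, acupuncture random | 0.25 / 0.34 / 0.46 toward LLLT | 0.05 / 0.03 / 0.01 |
| Opposite directions in the two arms | 0.36 / 0.66 / 0.87 toward LLLT | 0.03 / 0.02 / 0.02 |

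Entries are absolute values. Simulation error is about 0.77 / √800 = 0.03, so entries of that order are compatible with zero.

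**6. The mirror case, by a second simulation and by formula.** Here poor responders leave acupuncture, LLLT dropout is random, and the residual SD is assumed to be 4. If the worst 8 of 53 week-1 sleepers leave, the mean of those who remain shifts by φ(z)/(1 − p) with p = 8/53 = 0.151 and z = 1.03. That is 0.234 / 0.849 = 0.276 SD. The bias is 0.276 × r × 4 = 0.33 / 0.55 / 0.77 points against LLLT. A simulation of 4,000 trials gave 0.33 / 0.54 / 0.77. With milder logistic dropout it gave 0.16 / 0.25 / 0.38.

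**7. Consequence for the test.** Take the third row of the table. With bias b toward LLLT and standard error s, the chance of wrongly declaring LLLT superior is P(Z > 1.96 − b/s). For b = 0.25 and s = 0.765 this is P(Z > 1.63) ≈ 5%. For b = 0.46 and s = 0.755 it is P(Z > 1.35) ≈ 9%. The nominal value is 2.5%.

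**The case against.** Several counter-arguments have weight.

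- **The list is not closed.** The text says what the model will include, not that it includes nothing else, and a list of auxiliary variables is often left to an analysis plan, which is not shown here. A reader might infer that the plan excludes the diary and attendance. The document does not say so; it leaves them unnamed. What remains is that the article does state the model's contents, and that the natural reading of outcome data, given Table 3, does not reach items filed as process monitoring.
- **Much is already covered.** Week-6 ISI and the other week-2 scales count as available outcomes, so not everyone missing the week-2 ISI is affected. The baseline set is also wider than ISI and may explain some dropout. Neither point supplies post-baseline information for a participant lost for good before week 2.
- **The bias is conditional.** A reader might infer that the primary estimate is biased as planned. The document gives no dropout mechanism, and the bias is about 0 if dropout is random or works alike in both arms. Even the larger values in the mirror case (0.33 to 0.77) assume that exactly the 8 worst week-1 sleepers in one arm leave. This stands in full.
- **The near-perfect repair is partly built in.** The simulations let dropout depend on the diary and then gave the imputation a complete diary. Someone who leaves in the first week may return none. This stands too.
- **The diary's content is not described**, so any correlation with ISI is an assumption.

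**Conclusion.** The point holds as a minor improvement. No figure in the protocol is wrong, missing at random given baseline and arm is a permissible assumption, and 106 participants stands. For participants lost for good before week 2, however, the model as listed is in effect complete-case ANCOVA, while informative week-1 records that the trial schedules are not named.

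If dropout depends on early response in one arm only, the illustrative bias is 0.16 to 0.77 ISI points, or about 6% to 31% of the 2.5-point target (0.16 / 2.5 and 0.77 / 2.5). It can favour either arm. It reaches 0.87 if selection runs in opposite directions in the two arms. These values assume correlations of 0.3 to 0.7, a residual SD of 3.6 or 4, the dropout mechanisms shown, and the whole 15% lost before week 2. Fewer early losses would make the bias smaller.

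**What to change.** In the missing-data paragraph of the Statistical analysis section, or in the analysis plan if one exists, add before unblinding a sentence to this effect:

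> *The imputation model for week-2 ISI will also contain, as auxiliary variables, a summary of the week-1 sleep diary, the week-2 diary summary where present, and the number of sessions attended; missing auxiliary values will be imputed in the same procedure.*

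The diary summary should be defined at the same time, by staff blind to allocation. Week-6 ISI needs no addition, and the ANCOVA is unchanged.

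The cost is entry of diary data already scheduled, with no added participants or visits. Trial status reports that no comparative analysis has been done and that statisticians remain blinded, so the choice can still be prespecified. The downside is that the earliest leavers may have no diary, and that attendance partly restates dropout itself. The change would therefore reduce the bias rather than always remove it.
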